### Relevant concomitant care permitted or prohibited during the trial {11d}

During the recruitment and before each treatment session, the participants are asked not to participate in any concomitant interventions during the study.

All urgent interventions or treatments are recorded in the research documentation.

### Provisions for post-trial care {30}

Provisions for ancillary and post-trial care are not relevant to the study.

### Outcomes {12}

#### Primary outcome

There are three primary outcome measures in the study. Two of them assessed by means of behavioral self-report, visual analog scale (VAS) ratings of tinnitus for loudness and distress [72], and the third is performed by measuring the MML.

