**Methods:**

The intervention consists of bilateral high-definition tRNS (HD-tRNS) over the auditory cortex combined with the application of AS which is studied in a crossover design. The visits will be performed in 26 sessions. There will be 20 treatment sessions, divided into two blocks: active and sham HD-tRNS. Within the blocks, the interventions are divided into group A: HD-tRNS and AS, and group B: HD-tRNS alone. Furthermore, in addition to the assessments directly following the intervention sessions, there will be six extra sessions performed subsequently at the end of each block, after a period of some days (follow-ups 1 and 2) and a month after the last intervention (C). Primary outcome measures are analog scales for evaluation of subjective tinnitus loudness and distress, and the audiological measurement of minimum masking level (MML). Secondary outcome measures are brain activity as measured by electroencephalography and standardized questionnaires for evaluating tinnitus distress and severity.

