### Strategies to improve adherence to interventions {11c}

Participants will be contacted by phone and email, then appointments will be scheduled in advance according to the availability of each participant. In order to improve adherence, appointments will be available in three shifts, from Monday to Saturday.

The questionnaires will be collected on an easy-to-navigate online platform before each session at which the participants are present and in an online form in sessions 13 and 25. Additionally, after each therapy session, a safety questionnaire will be applied in order to identify any side effects resulting from the stimulation.

In case of non-compliance, such as absence in sessions, the participants will be contacted via telephone or email, and asked about continuation or early termination of the study.

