### Sample size {14}

Sample size calculations were conducted in G*Power 3.1.9 for the repeated measures, within-between interaction (ANOVA). The total sample size needed to detect a high assessment-by-treatment interaction effect (*f* = 0.25, beta = 0.95, alpha = .05, groups = 2, measurements = 5) is 32 participants. However, to compensate for a high estimated dropout rate of up to 25% during treatment, the aim is to recruit 40 participants leading to 20 participants per group.

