### Concealment mechanism {16b}

Randomization is performed on pseudonymized study codes with no name or other personal identifiers (i.e., sex, age in years, and tinnitus severity with the THI score).

Randomization is performed by the biometrician who is a researcher independent of the actual study procedures. The allocation list is kept in a separate file on the independent computer, only the biometrician has access to the document.

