## Statistical methods

### Statistical methods for primary and secondary outcomes {20a}

The distributions of the data will be assessed using measures of central tendency and measures of dispersion to determine the characteristics of tinnitus and describe other variables associated with the symptom.

The descriptive tinnitus data will be presented in tables, separated by intervention group. The safety parameters, adverse events, and laboratory assessments will be listed by participants and displayed in summary tables.

Finally, the assumptions of the independent and dependent variables will be evaluated. Parametric or non-parametric tests will be chosen based on the features of the data. These tests include the verification of absence of outliers through boxplot; homogeneity of variances in the independent variables through Levene test; and Mauchly’s test for sphericity, or if necessary, Greenhouse Geisser corrections.

The analysis will be performed using the statistic program R (https://www.r-project.org).

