#### Primary analysis

The data will be statistically analyzed for changes in subjective tinnitus loudness and distress (VAS) and MML by means of frequentist linear mixed-effect modelling (LME) by the biometrician after data collection has been completed.

Between- and within-subjects repeated measures ANOVA will be used to compare the effect of treatment pre and post, in both intervention groups.

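### Three unranked primary outcomes and two analyses named as primary rest on a sample size for one test at 0.05; if any one outcome counts as success, the family-wise error is about 8–14%

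*Protocol article*

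**What the plan says.** All references are to the protocol article.

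- **Primary outcome.** "There are three primary outcome measures in the study": VAS loudness, VAS distress and the minimum masking level (MML). The abstract lists the same three. Neither place ranks them or says whether one, any or all must succeed.
- **Sample size {14}.** The calculation is for one within-between interaction in a repeated-measures ANOVA, with f = 0.25 and "beta = 0.95, alpha = .05, groups = 2, measurements = 5". It gives 32 participants, raised to 40 for dropout of up to 25%. The 0.95 labelled beta is evidently the power. No outcome is named, and this is the only alpha in the document.
- **Primary analysis.** The three outcomes are analysed by "frequentist linear mixed-effect modelling (LME) by the biometrician after data collection has been completed". The next paragraph under the same heading adds a between- and within-subjects repeated-measures ANOVA of pre against post. Nothing says which of the two decides.
- **Statistical methods {20a}.** "Parametric or non-parametric tests will be chosen based on the features of the data", with reference to boxplots, the Levene test and Mauchly's test.
- **Concealment mechanism {16b}.** Of the allocation list, "only the biometrician has access to the document". Blinding {17a} covers participants and the researchers who treat and measure; it does not mention the analyst.
- **Intervention description {11a}.** The VAS scales are collected after treatment at sessions 11, 12 and 13, again at 23, 24 and 25, and at close-out (session 26). MML is collected at 12, 24 and 26.

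**The concern.** The stated alpha and sample size fit one test. The stated outcomes and analyses create several, and nothing printed says how they combine into one conclusion. If the trial may claim efficacy on whichever of the three outcomes reaches 0.05, the claim no longer carries a 5% error rate.

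Two further choices stay open until the data are in: which of the two analyses decides, and whether a parametric or non-parametric test is used. The person named to run the primary analysis is also the only one with the allocation list. That does not show that the choices will be made with allocation in view, but nothing in the text prevents it, and a reader of a positive result could not rule it out.

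**Working it through.** **Inputs.** From Sample size {14}: f = 0.25, alpha = 0.05, power 0.95, k = 2 groups, m = 5 measurements, N = 32, 40 to be recruited, dropout 25%. From Primary outcome: three outcomes. Assumed, because the document does not give them: correlation between repeated measurements rho = 0.5, sphericity epsilon = 1, and the correlation r among the three outcomes (0 to 0.9 examined).

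**Step 1: reproduce the plan's figure.** For the within-between interaction:

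- lambda = f² × N × m / (1 − rho) = 0.0625 × 32 × 5 / 0.5 = 20.0
- df1 = (k − 1)(m − 1) = 4
- df2 = (N − k)(m − 1) = 30 × 4 = 120
- power at alpha 0.05 = 95.7%

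At N = 30 the same formula gives 94.3%, so 32 is the smallest even total reaching 95%. The stated 32 reproduces exactly, for one test at an undivided 0.05.

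**Step 2: error rate if any one of three outcomes counts.** Independent outcomes: 1 − (1 − 0.05)³ = 1 − 0.857 = 14.3%. For three two-sided normal tests with common correlation r:

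| r | Family-wise error |
|---|---|
| 0 | 14.3% |
| 0.5 | 12.5% |
| 0.7 | 10.9% |
| 0.8 | 9.8% |
| 0.9 | 8.4% |

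Simulating the plan's own type of test (three omnibus interaction F tests, N = 32, five measurements) gives much the same: 14.2% at r = 0, 13.0% at 0.5, 11.1% at 0.7 and 10.0% at 0.8.

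**Step 3: cost of control.** Holm's strictest step is 0.05 / 3 = 0.0167. Putting this alpha into the Step 1 formula:

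| Evaluable N | Power at 0.05 | Power at 0.0167 |
|---|---|---|
| 32 | 95.7% | 89.8% |
| 30 (= 40 × 0.75) | 94.3% | 87.1% |
| 40 (no dropout) | 98.7% | 96.3% |

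Reaching 95% at 0.0167 takes 38 evaluable participants (95.2%), or 38 / 0.75 = 50.7, so 51 recruited.

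**The case against.** The strongest reply is that this is a condensed article. The full protocol and any analysis plan are not shown, and multiplicity rules are often placed there. Nor does any sentence say that each outcome is tested at 0.05 or that one success is enough; if all three had to succeed, the error would be at most 5%. That is fair, and it is why the error figures are conditional. It does not remove the point: unranked outcomes, two analyses under one primary heading, a data-driven test choice and a sample size for a single test are all stated on the page. An adjustment placed elsewhere would still meet a sample size calculated without it.

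Four stronger readings are tempting but not supported.

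- **Separate sessions.** A reader might count seven tests per block (two VAS scales at three sessions plus MML once) and reach 1 − 0.95⁷ = 30% for independent tests. The plan does not say that sessions are tested separately. Its sample size uses one omnibus interaction over five measurements, and collecting data at several sessions is not in itself multiplicity.
- **Rival tests as a source of error.** A mixed model and a repeated-measures ANOVA on the same data agree closely, so choosing between them adds little to the error rate. The harm is that the deciding test is undefined.
- **The biometrician picks the test.** Statistical methods {20a} is in the passive and ties the choice to assumption checks. That an analyst who knows the allocation makes it is an inference from combining sections, so it is a risk and not a stated procedure.
- **A timing conflict at session 11.** Questionnaires are collected "before each session at which the participants are present", while the abstract mentions assessments directly after intervention sessions. The latter can be read as the safety questionnaire, so the two are compatible.

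**Conclusion.** The point holds in a limited form. As printed, the plan declares three primary outcomes and two primary analyses on a sample size for one test at 0.05. If any one outcome significant at 0.05 counts as success, the family-wise error is about 8–14% over assumed correlations of 0.9 down to 0. It would exceed that range only if post-treatment sessions were also tested separately, and would be 5% or less if all three outcomes were required; the document settles neither. Testing each outcome at 0.05 is inferred from the single alpha in the sample-size section. The analyst's access to the allocation list makes the open choices more exposed, but is not evidence of bias.

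**What to change.** 1. Name one deciding test: the linear mixed model with one pre-specified contrast (for example the arm-by-stimulation interaction), either at one pre-specified post-treatment session or jointly over all of them. Sessions 12 and 24 are the first post-treatment sessions with all three outcomes, which makes them a natural choice but not the only defensible one.
2. Make the repeated-measures ANOVA a sensitivity analysis and delete the data-driven choice between parametric and non-parametric tests.
3. Control the three outcomes at an overall 0.05, by Holm or by a fixed testing order.
4. Lock the analysis script before the allocation is merged with the outcome data.

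No visit or measurement changes, but the power statement must. Under Holm's strictest step, and with the assumed rho and epsilon, it is 89.8% at 32 and 87.1% at 30 evaluable participants, against the stated 95%; keeping 95% would mean recruiting about 51. A fixed order avoids this loss for the first outcome only, since later outcomes are tested only if the earlier ones succeed. All these figures belong to the five-measurement omnibus interaction; a single-session contrast needs its own power calculation.

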#### Secondary outcome

The secondary outcome is resting state and event-related EEG potentials [40] recorded for that purpose.

#### Other outcome of interest

The other outcomes will be used in order to describe and characterize the study sample, control variables and correlational analyses. These will be assessed only on the second visit, before the first treatment (Fig. 4).

**Fig. 4 Fig4:**
[figure not shown]
Schedule of enrolment, interventions, and assessments. Adapted of SPIRIT, 2013

To complete primary and secondary outcomes, the standardized Tinnitus Case History Questionnaire [72], physical health, psychological health [73–75, 77, 79, 80], and personality questionnaires [76, 81], as well as standardized tinnitus and hyperacusis questionnaires [72, 82–86] are assessed. Audiometry and tinnitometry complement this set of outcomes.

##### Tinnitus and hyperacusis

Tinnitus Sample Case History Questionnaire (TSCHQ) [72]Tinnitus Functional Index (TFI) [78, 83]Tinnitus Handicap Inventory (THI) [84, 85]Geräusch-Überempfindlichkeits-Fragebogen (GÜF) [86]

##### Audiometry/tinnitometry

Pure tone audiometry (PTA)Pitch matching (PM)Minimum masking level (MML)Isometric forward masking contour (IFMC)Temporal masking curve (TMC)Sensation level (SL)Loudness discomfort level (LDL)Residual inhibition (RI)

##### Physical and psychological health

Beck-Angst-Inventar (BAI) [73, 77]Beck-Depressions-Inventar (BDI) [74, 79]World Health Organization Quality of Life (WHOQoL) [75, 80]

##### Personality

Big Five Inventory (BFI-2) [76, 81]

### Participant timeline {13}

Participants will receive 20 days of therapy, 10 days with active current, and 10 days sham stimulation.

Before each block, primary, secondary, and other outcomes will be assessed. In addition, two follow-ups will be performed, with 2 days of assessments each. Finally, there will be a close-out, with complete evaluation of all outcomes (Fig. 4).

### Sample size {14}

Sample size calculations were conducted in G*Power 3.1.9 for the repeated measures, within-between interaction (ANOVA). The total sample size needed to detect a high assessment-by-treatment interaction effect (*f* = 0.25, beta = 0.95, alpha = .05, groups = 2, measurements = 5) is 32 participants. However, to compensate for a high estimated dropout rate of up to 25% during treatment, the aim is to recruit 40 participants leading to 20 participants per group.

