### Criteria for discontinuing or modifying allocated interventions {11b}

Given the general low risk associated with the study procedures, no realistic scenario of withdrawal or discontinuation can be drawn for this study. Although risk is not commonly reported with the current therapy, participants will be monitored in case they experience any symptoms. The probability exists for some minor side effects exists, as reported in the literature, such as nausea, tingling, headache, tiredness or irritating sensation, difficulty in concentration, redness, or pain [18].

In any case, participants may terminate their participation in the study at any time and without any justification. They will be registered as dropouts and will not be taken into account in the analysis.

All participants will be informed in writing on the information sheet and on the informed consent form, and verbally in the interview prior to enlisting in the study, that they may terminate their participation in the study at any time and without justification. After withdrawal, the participants will be contacted for a debriefing interview. Dropouts will be replaced in order to achieve the intended sample size whenever possible. Replacement will be performed along the established selection and allocation criteria.

Compliance is usually high, as has been observed in former studies of our group [70, 71], and other groups in the field of tinnitus research. This is true even in the absence of monetary incentives and possible detrimental effects on the condition. Therefore, no specific measures are considered to increase compliance.

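### Recruiting 40 leaves 30 participants at the stated 25% dropout, not the 32 the plan requires; 40 covers a dropout of at most 20%

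*Protocol article*

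**What the plan says.** The Sample size {14} section of the protocol article names the method: "Sample size calculations were conducted in G*Power 3.1.9 for the repeated measures, within-between interaction (ANOVA"). Its inputs are an effect size f = 0.25 and "beta = 0.95, alpha = .05, groups = 2, measurements = 5", and the result is given as "measurements = 5) is 32 participants". The section then allows for losses: "to compensate for a high estimated dropout rate of up to 25% during treatment, the aim is to recruit 40 participants". These are to be split evenly, 20 to each arm.

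Two statements under Criteria for discontinuing or modifying allocated interventions {11b} bear on what happens to those losses. On participants who end their participation: "They will be registered as dropouts and will not be taken into account in the analysis". On replacement: "Dropouts will be replaced in order to achieve the intended sample size whenever possible". The section on protocol non-adherence and missing data {20c}, by contrast, commits the efficacy analyses to intention to treat and keeps participants who stopped treatment in their randomised arm.

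**The concern.** The recruitment figure is presented as the one that protects the requirement of 32 against a loss of up to a quarter of the participants. Losing a quarter of 40 leaves 30, so the requirement, the dropout allowance and the recruitment target cannot all be right.

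At stake is whether the trial keeps its planned power at the dropout it says it allows for. The sentence is also likely to be carried into the results paper and used there to judge whether the target was met.

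The label on the power figure adds a smaller fault. Beta is the type II error rate, so a beta of 0.95 means a power of 0.05.

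**Working it through.** **Inputs from Sample size {14}:** f = 0.25; alpha = 0.05; k = 2 groups; m = 5 measurements; 0.95 read as power; required N = 32; dropout d = 0.25; recruitment 40, 20 per group.

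**Assumed, because not stated:** correlation between repeated measures rho = 0.5; sphericity (epsilon = 1).

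**Step 1. Reproduce the 32.** For the within-between interaction:

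- noncentrality lambda = f² × N × m / (1 − rho)
- df1 = (k − 1)(m − 1) = 4
- df2 = (N − k)(m − 1) = 4(N − 2)

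At N = 32, lambda = 0.0625 × 32 × 5 / 0.5 = 20.0 and df2 = 120, which gives power 0.957. Searching even totals, 32 is the smallest that reaches 0.95. The plan's figure is therefore reproduced, with 0.95 as power and not as beta. Other correlations do not return it: the smallest even total is 44 at rho = 0.3, 38 at 0.4 and 26 at 0.6.

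**Step 2. Reproduce the 40.**

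- Adding the rate: N × (1 + d) = 32 × 1.25 = 40. This matches the plan.
- Dividing by the retained share: N / (1 − d) = 32 / 0.75 = 42.67, so 43, or 44 (22 per group) for equal groups. Check: 44 × 0.75 = 33, which is at least 32.

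**Step 3. What 40 delivers.**

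- At 25% dropout: 40 × 0.75 = 30 remain, 15 per group if losses are equal. The shortfall is 32 − 30 = 2.
- Largest dropout that still leaves 32: 1 − 32/40 = 20%.

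**Step 4. Power at the numbers that remain** (rho = 0.5, epsilon = 1):

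| N analysed | lambda | df2 | Power |
|---|---|---|---|
| 32 | 20.0 | 120 | 0.957 |
| 31 | 19.375 | 116 | 0.950 |
| 30 | 18.75 | 112 | 0.943 |

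**Step 5. Dependence on the assumptions.** At N = 30, power is 0.83 at rho = 0.3, 0.89 at 0.4, 0.94 at 0.5 and 0.98 at 0.6. At rho = 0.5 with epsilon = 0.75 it is 0.88. The unstated correlation and sphericity move power far more than the loss of two participants does. Steps 2 and 3 need neither assumption.

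**The case against.** The strongest reply is that 40 is not a closed cohort. Section {11b} provides for replacement of dropouts, so 30 would be reached only if dropout passed 20% and replacement also fell short. That lowers the practical risk. But replacement is promised only where possible, and the sample size section does not rely on it: it offers the 40 itself as the compensation. Replacement does not make the calculation right.

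A second reply is that section {20c} keeps discontinued participants in the analysis, and the planned linear mixed-effects model can use partial data, so a dropout need not be lost altogether. Section {11b} says the reverse, that dropouts are left out. The two sections conflict and should be reconciled. The figure of 30 analysed follows from {11b}, and it is also the reading on which a dropout allowance makes sense. Under {20c} the participants would stay, but some of their outcome data would be missing or imputed, and that is not the information of 32 complete participants.

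Third, the 25% is an upper limit and the 40 an aim, so nothing is strictly guaranteed, and the gap exists only for dropout above 20%. That is true, but the text says the allowance works up to that limit, and at the limit it does not.

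Finally, the effect is small and the meaning of the beta label is plain from context. Both points stand, and they are why a corrected statement is enough.

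**Conclusion.** The concern holds. The dropout allowance was computed by adding 25% instead of dividing by 0.75, so the recruitment target covers a dropout of 20%, not the 25% stated. The size is two participants at the upper limit of dropout. In power it is a fall from 95.7% to 94.3%, or 0.7 percentage points below the 95% target, if rho = 0.5 and sphericity hold. The participant counts follow from the protocol's own numbers, taking dropouts as lost to the analysis; the power figures rest on the two assumed values. The beta label is a notation error with no effect on the calculated 32. No conclusion of the trial is likely to turn on this, but a sample size statement the trial relies on is wrong as written and should be corrected.

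**What to change.** Rewrite the end of the sample size section along these lines: 32 participants give power = 0.95 (correlation between repeated measures 0.5 and sphericity assumed); recruiting 40 leaves 32 at a dropout of 20%; at a dropout of 25%, 30 remain and power is about 94% under the same assumptions. The investigators should confirm the correlation and sphericity values they entered in G*Power and print those. Replace the beta label with power.

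The cost is one corrected statement, with a slightly less favourable figure and no extra recruitment. If the investigators prefer to keep the 25% allowance with at least 32 remaining, the target becomes 43, or 44 for equal groups, which is four more than planned.

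When making the change, reconcile {11b} with {20c} on whether dropouts are analysed, because the number remaining depends on it.
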